### Research objectives

1.1.

Objectives of the observational study:
Replicate findings of HPA-axis dysregulation in PTSD patients relative to a control group of individuals without PTSD or history of early-life trauma.Investigate associations between history of ELA and HPA-axis dysregulation.Investigate whether epigenetic markers of glucocorticoid signalling (such as methylation status of glucocorticoid-related genes) mediate the association between history of ELA and HPA-axis dysregulation.Exploratively, investigate whether HPA-axis dysregulation and glucocorticoid signalling are associated with treatment response.

Objectives of the pharmacological intervention study:
Investigate whether patients with HPA-axis dysregulation show impairments in extinction learning relative to patients without HPA-axis dysregulation, and whether this is accompanied by different neural responses during extinction learning in brain regions associated with fear expression and extinction.Investigate whether the subgroup of PTSD patients with HPA-axis dysregulation particularly benefits from hydrocortisone administration (versus placebo) to improve the strength and generalization of extinction memories.Investigate neural responses during extinction learning in brain regions associated with fear expression and extinction after hydrocortisone administration (versus placebo), that may be associated with improvements in strength and generalization of extinction learning.

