##### Primary outcome measures

2.6.2.1.

Successful fear acquisition, as indicated by a higher SER for the CS+s in comparison to CS− in the last block of the fear acquisition task, is a prerequisite for the assessment of extinction learning. During the fear extinction task, fear extinction should be indicated by decreasing SER, showing no expectancy of shock in the last block of this task. Fear acquisition and fear extinction will also be signalled by psychophysiological outcome measures (SCR and PDR). Neuroimaging during the fear extinction task investigates pharmacological effects on neural responses associated with fear extinction learning. Ultimately, the strength and generalization of the fear and extinction memories are assessed in the extinction recall task during recall of these memories upon presentation of the CSs in different contexts. Here, the primary outcome variables are SCR, PDR, and SER. Details of psychophysiological analyses are described in Supplementary Material S13. More specifically, increased strength of extinction memory should be indicated by smaller differential responses within the extinction context, whereas increased generalization of extinction memory should be indicated by a context interaction effect showing transfer of extinction to novel and/or acquisition contexts. In addition, effects of HPA-axis dysregulation are investigated to investigate their role in glucocorticoid effects on extinction recall. Relative suppression of the CAR from the DST is prespecified as the primary outcome measure, and based on a median split, the PTSD group will be divided over two subgroups. Grouping based on other HPA-axis outcome variables will be regarded as secondary and subjected to appropriate multiple-comparison corrections. Planned MRI (preprocessing) analyses are discussed in the Supplementary Material (S14).

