##### Statistical modelling

2.6.2.2.

1. Investigate whether patients with HPA-axis dysregulation show impairments in extinction learning relative to patients without HPA-axis dysregulation, and whether this is accompanied by different neural responses during extinction learning in brain regions associated with fear expression and extinction.

This objective will be investigated with data from placebo sessions only. At the psychophysiological level, we expect HPA-axis dysregulation to be associated with lower strength of the extinction memory, indicated by lower differential responses for CS+U vs CS+E and/or higher differential responses for CS+E vs CS− during the extinction recall task. This will be modelled with a two-way ANOVA of averaged differential responses during the first block, which is within the extinction context and contains two presentations of each CS. Higher generalization of the extinction memory for the HPA-axis normalized group would be indicated by a context interaction effect that shows less renewal of fear, i.e. a lower increase of differential effects upon stimulus presentations within the novel and acquisition contexts. These comparisons may be affected by an overall attenuation of fear responses due to re-extinction over the course of the extinction recall task. This effect will be investigated with a 2 (group) by 3 (context) mixed ANOVA of averaged differential responses during the first block of each context. Both models will include the covariate order of medication administration, and, if appropriate, the covariates age and gender. Outcome measures SCR, PDR, and SER will be included in separate models, but since these measures of conditioning are complementary, no multiple comparisons correction will be applied. At the level of neuroimaging, differences in extinction learning signalled during the fear extinction task could be underlying the differences at the behavioural level. Here, we would expect different neural responses in brain regions and networks associated with (context-dependent) extinction learning for patients with HPA-axis dysregulation, which could also be associated with less successful recall of the extinction memory.

2. Investigate whether the subgroup of PTSD patients with HPA-axis dysregulation particularly benefits from hydrocortisone administration (versus placebo) to improve the strength and generalization of extinction memories.

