To answer the main objective of the pharmacological intervention study, the aforementioned psychophysiological models will be extended with data from the hydrocortisone sessions (thus adding a within-subjects category for medication). Period effects may follow from the crossover design and will be accounted for by defining a medication-by-order interaction effect. Based on previous research, we hypothesize a group-by-medication interaction effect, indicating greater strength and/or generalization of the extinction memory following administration of hydrocortisone, that is most pronounced for the HPA-axis dysregulation group.

3. Investigate underlying neural mechanisms of glucocorticoid administration (versus placebo) to improve extinction learning.

Recruitment of neural networks associated with (context-dependent) extinction learning for patients with HPA-axis dysregulation (see point 1 above) would be expected to enhance following hydrocortisone administration. Pharmacological effects and their potential interactions with HPA-axis dysregulation are primarily investigated during the extinction learning task, but will also be supported by the following analyses: (1) amygdala (and salience network) reactivity to the emotion processing task, which we expect to be reduced after hydrocortisone administration; and (2) resting-state connectivity in networks associated with (context-dependent) extinction learning – ventromedial prefrontal cortex–amygdala connectivity, in particular – which we expect to be enhanced after hydrocortisone administration.

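### Part B objective 1 asks about extinction learning, but both of its behavioural models use only next-day recall, so they cannot show whether extinction was less well learned or less well retained

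*Protocol article*

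**What the plan says.** The Protocol article, Section 1.1, states the first part B objective as: "Investigate whether patients with HPA-axis dysregulation show impairments in extinction learning relative to patients without HPA-axis dysregulation". Section 2.6.2.2 repeats it and adds: "This objective will be investigated with data from placebo sessions only".

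The same section then names two behavioural models.

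- **Strength of the extinction memory.** The expected pattern in the dysregulated group is a smaller CS+U v CS+E difference "and/or higher differential responses for CS+E vs CS− during the extinction recall task". The model is: "This will be modelled with a two-way ANOVA of averaged differential responses during the first block, which is within the extinction context".
- **Generalization.** The model is a "2 (group) by 3 (context) mixed ANOVA of averaged differential responses during the first block of each context", where the blocks are again those of the recall task.

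On adjustment, the section says: "Both models will include the covariate order of medication administration, and, if appropriate, the covariates age and gender". The response level at the end of extinction is not among the covariates.

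For the extinction phase itself, Section 2.6.2.1 gives an expectation: "fear extinction should be indicated by decreasing SER, showing no expectancy of shock in the last block of this task". It adds that SCR and PDR will also signal extinction. Neither section states a comparison of these measures between the HPA-axis groups. Group differences during extinction appear only on the imaging side of objective 1.

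For objective 2, Section 2.6.2.2 says that "the aforementioned psychophysiological models will be extended with data from the hydrocortisone sessions".

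**The concern.** Extinction learning takes place on day 1, in four blocks without shock. Recall is tested the next day. A patient who still responds to CS+E at recall may never have finished extinguishing, or may have extinguished fully and lost it overnight. Both are plausible in this population. The Introduction names inability to learn safety as a hallmark of PTSD, and it also discusses incomplete extinction and return of fear.

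Objective 1 names the first of these mechanisms, while its behavioural models measure the sum of the two. Randomization does not help here. The drug order is counterbalanced, but the groups come from a median split on cortisol suppression, so nothing makes their end-of-extinction levels alike.

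At stake is whether the trial can answer objective 1 as it is worded. The imaging analysis also looks for group differences in the extinction phase that might underlie the behavioural result. As printed, it has no stated behavioural group comparison from that phase to stand beside it.

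**Working it through.** The article gives no figure to reproduce on this point. Effect size, SD, alpha and power are left to Supplement S3, which is not shown. The check is a comparison of objective with models, followed by an illustration.

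**1. Which data enter the models (Section 2.4.5.1)**

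| Phase | Trials per CS | In a stated behavioural group model? |
|---|---|---|
| Extinction, day 1 | 4 blocks × 4 = 16 for CS+E and 16 for CS− | No |
| Recall, first block, day 2 | 2 | Yes, both models |
| Recall, first block of each of three contexts | 3 × 2 = 6 | Yes, generalization model |

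SCR and PDR are recorded in every phase (Section 2.4.5), and SER in all tasks (Figure 2 legend). The start-to-start interval from extinction to recall is at least 24 hours (Section 2.5.5.2).

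**2. Why recall alone cannot separate the mechanisms**

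Write the CS+E minus CS− response at recall as Y = E + R, where E is what remains at the end of extinction and R is the overnight change. With invented values:

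- Unequal learning, equal retention: 0.2 + 0.2 = 0.4 and 0.5 + 0.2 = 0.7, a gap of 0.3.
- Equal learning, unequal retention: 0.2 + 0.2 = 0.4 and 0.2 + 0.5 = 0.7, the same gap of 0.3.

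A model of Y without E returns the same answer in both cases. The CS+U v CS+E contrast does not resolve this. It separates extinction from general retention of fear, not learning of extinction from retention of extinction.

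**3. Simulation**

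Inputs from the article: 80 participants in part B (Section 2.2) and a median split (Section 2.6.2.1), taken as 40 v 40. Assumptions: two-sided alpha of 0.05; E and R independent and normal with variance 0.5 each, so that Y has SD 1; two-sample t-tests; 20,000 replicates.

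The difference detectable with 80% power is (1.960 + 0.842) × √(2/40) = 0.626. A total deficit of 0.63 was used, for which power is 0.804.

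| Source of the 0.63 deficit | Mean gap at recall | Recall test rejects | End-of-extinction test rejects | Change test (Y − E) rejects |
|---|---|---|---|---|
| Learning only | 0.63 | 79.4% | 97.6% | 5.0% |
| Retention only | 0.63 | 79.5% | 4.9% | 97.6% |
| Half each | 0.63 | 80.0% | 49.8% | 50.6% |

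The recall column does not move with the mechanism. The end-of-extinction column does. The percentages depend on the assumed variances. The sameness of the recall column follows from Y = E + R and the equal variances; with unequal variances the recall gap and its test would still be the same, because only the total variance of Y enters.

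**The case against.** The strongest reply is that this is mostly terminology. In Section 2.6.2.2 the behavioural inference drawn from recall is a weaker extinction memory, and a memory that is weaker because less was learned is still weaker. The article also uses extinction learning loosely, as an umbrella that covers its recall outcomes. This stands in part. A reader might infer that the plan would report a retention deficit as a learning deficit, but the text does not commit to that. What remains is that objective 1, as worded, has no behavioural test of its own. Rewording the objective would remove the mismatch but leave the learning question unanswered.

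A second reply is that Supplement S13 holds details of the psychophysiological analysis and may contain an extinction-phase model. It is not shown, so this cannot be excluded. However, the main text itself names the models for objective 1, and those are recall models.

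Three stronger readings are tempting, and the document does not support them.

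- **That objective 2 has the same fault.** It does not. Objective 2 concerns how strong the extinction memory is and how far it generalizes, and next-day recall measures that directly.
- **That the study cannot separate learning from retention.** This is true only of the two ANOVAs. SCR, PDR and SER are all recorded during extinction.
- **That recall is interpreted as if every participant had extinguished completely.** Section 2.6.2.1 says what extinction should look like; it does not make that an assumption of the recall models.

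There is also a fair warning about the remedy. A change score from the last extinction block to recall compares scanner with laboratory recordings. In any drug comparison it would also subtract a value measured after dosing, and so remove part of an effect that acts through learning.

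**Conclusion.** The point holds for objective 1 only. Its behavioural models can show a weaker extinction memory in the dysregulated group, but not whether extinction was less well learned or less well retained. None of the 16 CS+E and 16 CS− extinction trials per session enters a stated behavioural group comparison.

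This conclusion rests on the article's own wording of the objective and the models. The simulated rejection rates are illustrative and rest on assumed variances, alpha and effect size. It should be put right before analysis but does not threaten the main objective of part B.

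**What to change.** In Section 2.6.2.2, objective 1:

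1. Add a group-by-block model of CS+E v CS− over the four extinction blocks, in placebo sessions, with SCR, PDR and SER in separate models. Base any statement about impaired extinction learning on this model.
2. Keep the two recall ANOVAs as the test of strength and generalization of the extinction memory.
3. As a supportive analysis only, report the recall group difference alongside the level in the last extinction block. Use SER, or SCR and PDR standardized within phase, because scanner and laboratory scales differ.

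Leave objective 2 as it is. A model of the extinction phase with medication and group-by-medication terms may be reported as support for the mechanism in objective 3. A change score from a post-dose value should not be the deciding test.

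The cost is a few extra models on data the study already records. One limitation is that SER may sit at its floor by the last extinction block, in which case it will say little about group differences there and SCR and PDR will carry more of the weight.

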### Population

2.2.

This study aims to include *n *= 160 people with PTSD (part A), half of whom participate in the entire study (*n = *80 for part B). In addition, *n *= 30 control group participants are recruited (part A). All participants must be aged 18–64 years old. Exclusion criteria for both groups are listed in Table 1. More details on criteria assessed during the screening visit and amendments during the trial are listed in the Supplementary Material (S1 and S2). Power calculations are also described in the Supplementary Material (S3).

**Table 1. T0001:** Exclusion criteria.

Group	Exclusion criteria
PTSD	General exclusion criteria:
	- Current psychotic or manic episode
	- Benzodiazepine medication: Daily intake of benzodiazepines, or otherwise irregular intake of benzodiazepines (‘when needed’) but unable to withhold intake according to study procedures Exception: low evening doses (sleep medication)
	- For part B only: MRI contraindications
	Criteria assessed during screening session:
	- Does not receive a classification of current PTSD according to clinical interview assessment
Control	General exclusion criteria:
	- Current or past psychiatric disorder
	- Use of psychotropic medication
	- History of childhood maltreatment
	Criteria assessed during screening session:
	- Early-life adversity according to questionnaire assessment
	- (History of) psychiatric disorders according to clinical interview assessment
Both	General exclusion criteria:
	- General learning disability or intellectual disability
	- Body mass index > 35 kg/m^2^
	- Pregnancy or breastfeeding
	- Substance use: Unable or unwilling to withhold recreational drug use and limit alcohol use according to study procedures
	- Nicotine smoking: Unable or unwilling to discuss frequency and timing of smoking according to study procedures
	- Glucocorticoid medication/supplements: Current or recent regular use of systemic corticosteroids (< 1 month ago). For non-systemic corticosteroids, average use of more than once a week and/or no possibility to withhold according to study procedures
	- Hypersensitivity to glucocorticoids
	Criteria only if relevant to study outcomes or feasibility of study procedures:
	- Relevant neurological disorder
	- Severe physical disorder
	- Relevant endocrine disease and/or current or recent endocrine treatment

Note: MRI = magnetic resonance imaging; PTSD = post-traumatic stress disorder; BMI = body mass index.

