#### Fear conditioning and extinction task

2.4.5.

To assess the strength and generalization of safety learning within an experimental setting, the current study employs a 2 day differential fear acquisition, extinction, and extinction recall task in a virtual environment (VE) with contexts as occasion setters (Figure 2). This task was adapted from previous studies and subsequently validated in a study with healthy young adults (de Nooij et al., 2021; de Voogd et al., 2020; Wirz et al., 2021). The task consists of two different VEs (natural scene and city scene) to allow repeated measurements within the crossover design of this study. Contexts for experiences are defined by three different houses within each VE. The conditioned stimuli (CSs) are simple geometric shapes and the unconditioned stimulus (US) is an electric shock to the fingers. The task consists of three phases: (1) fear acquisition, (2) fear extinction, and (3) recall. In each phase, the participant navigates within the three-dimensional VE using a joystick. After navigating to one of the houses, the participant is presented with a trial block of a two-dimensional task. During each trial, the participant provides a shock expectancy rating (SER) on a scale from 1 (‘certainly no shock’) to 5 (‘certainly a shock’). Primary outcomes consist of fear-related measures of autonomic nervous system response, particularly the skin conductance response (SCR) and pupil dilation response (PDR); these are assessed during each phase of the task. Further details on the task, experimental set-up, and counterbalancing are outlined in the Supplementary Material (S9).

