##### MRI visit (B1.1 and B2.1)

2.5.5.1.

In the psychophysiology laboratory, the participant completes the two practice tasks (see Section 2.4.5) in the presence of the researcher. If more practice is needed, a practice test is repeated. The intensity of electric shocks is determined by a calibration procedure (for details, see Supplementary Material S9). The participant then performs the fear acquisition task with psychophysiological assessment (pupil, skin conductance, heart rate). After a lunch break, the participant completes several online questionnaires, followed by a practice session in the dummy MRI laboratory and a second break. Subsequently, they provide a baseline saliva sample, which is followed by the oral intake of the study medication (indistinguishable capsule with 20 mg hydrocortisone or placebo). During the experimental set-up for the MRI session, the participant provides another saliva sample 30 minutes after medication administration. Heart rate and respiratory data are collected throughout the MRI session. The first part of the MRI session consists of a field map and task-based fMRI during fear extinction (45–55 minutes after medication administration) with psychophysiological assessment (pupil, skin conductance, heart rate). This is followed by a structural scan (T1-weighted during the first session; diffusion tensor imaging during the second session). During a short break, another saliva sample is provided (60–75 minutes after medication administration). The second part of the MRI session consists of resting-state fMRI with field mapping, and task-based fMRI during emotion processing with field mapping.

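### The recall models leave out each session's pre-drug acquisition response, so the non-randomised objective 1 comparison on CS+E vs CS− can confuse conditioning strength with extinction memory; objective 2 loses at most precision

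*Protocol article*

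**What the plan says.** Section 2.6.2.2 of the protocol article describes two recall models for objective 1, both on placebo sessions. One is an ANOVA of averaged differential responses in the first extinction-context block; the other is a group-by-context mixed ANOVA. Their covariates are listed: "Both models will include the covariate order of medication administration, and, if appropriate, the covariates age and gender". For objective 2, "the aforementioned psychophysiological models will be extended with data from the hydrocortisone sessions", with a medication factor and a medication-by-order term. No acquisition response appears in either set.

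The groups come from dexamethasone suppression of the awakening response: "based on a median split, the PTSD group will be divided over two subgroups" (Section 2.6.2.1). They are not randomised.

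Acquisition responses exist for every session. Section 2.4.5 says of skin conductance (SCR) and pupil dilation (PDR) that "these are assessed during each phase of the task"; shock expectancy (SER) is rated on every trial. Section 2.5.5.1 puts acquisition early in the MRI visit, "The participant then performs the fear acquisition task with psychophysiological assessment", with capsule intake only later that day.

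Acquisition enters the analysis text in one place as a condition. Section 2.6.2.1 defines it on expectancy ratings alone: "Successful fear acquisition, as indicated by a higher SER for the CS+s in comparison to CS− in the last block of the fear acquisition task". The article then says that meeting this condition "is a prerequisite for the assessment of extinction learning". It does not say what happens to a session or person that fails it.

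**The concern.** Responding at recall depends on two things: how strongly fear was conditioned, and how well the extinction memory is retained and expressed. The plan reads a smaller differential response in the extinction context as stronger extinction memory. On CS+E vs CS−, weaker conditioning produces the same picture.

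Randomisation does not protect objective 1, because its groups are defined by cortisol regulation. The article's own premise is that glucocorticoids strengthen emotional memories, so a difference between these groups in acquiring fear is plausible. An apparent extinction deficit could then be a conditioning difference. The covariates listed do not address this: order, age and gender do not measure conditioning strength in that session. In objective 2, age and gender are also constant within a patient, so as main effects they cannot sharpen a within-patient drug contrast, whereas a session-specific baseline can.

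**Working it through.** **Inputs.** Part B has 80 participants (Section 2.2: of the 160 with PTSD, "half of whom participate in the entire study"). A median split taken within part B gives about 40 vs 40. The article states no alpha, power, effect size or SD (power is referred to Supplement S3), so there is no figure to reproduce. Two-sided alpha of 0.05 is assumed. Also assumed are *r*, the within-session acquisition–recall correlation, and *g*, the group gap in acquisition in SD units.

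**1. Direction of each contrast.** Let conditioning strength be F, rising from 1.0 to 1.3.
- If extinction removes 60% of it, CS+E − CS− = 0.4F goes from 0.40 to 0.52 (looks like weaker extinction), and CS+U − CS+E = 0.6F goes from 0.60 to 0.78 (looks like stronger extinction).
- If extinction removes a fixed 0.6, CS+E − CS− = F − 0.6 goes from 0.40 to 0.70, and CS+U − CS+E stays at 0.60.

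The false deficit therefore arises only on CS+E vs CS−. On CS+U vs CS+E a real deficit could be hidden, or nothing changes.

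**2. Objective 1.** Spurious difference d = r × g, with SE = √(2/40) = 0.224. Type I error = 1 − Φ(1.96 − d/SE) + Φ(−1.96 − d/SE). Simulation (6,000 runs per setting, with group and order in the model) checks this with and without the covariate.

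| r | g | d (SD) | Formula | Simulated, no covariate | Simulated, with covariate |
|---|---|---|---|---|---|
| 0.3 | 0.3 | 0.09 | 0.069 | not run | not run |
| 0.5 | 0 | 0 | 0.050 | 0.049 | 0.055 |
| 0.5 | 0.3 | 0.15 | 0.103 | 0.100 | 0.052 |
| 0.5 | 0.5 | 0.25 | 0.201 | 0.207 | 0.050 |
| 0.7 | 0.5 | 0.35 | 0.347 | 0.342 | 0.049 |

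The simulation lets recall depend on acquisition as measured. A noisy acquisition score would correct only part of the distortion.

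**3. Objective 2, bias.** In the same simulations (no drug effect, order balanced within groups), the group-by-medication test on drug-minus-placebo differences had a type I error of 0.047 to 0.053 without the covariate and 0.048 to 0.052 with it. Without the covariate, the mean estimate lay between −0.005 and 0.005. The stable part of conditioning cancels within the patient.

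**4. Objective 2, precision.** Let ρ be the correlation between the within-patient session *differences* in acquisition and in recall. The residual SD falls by the factor √(1 − ρ²). For an effect of 0.626 SD of the within-patient difference (80% power unadjusted, 40 vs 40), power becomes 0.84 at ρ = 0.3, 0.90 at ρ = 0.5 and 0.98 at ρ = 0.7.

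ρ is not the within-session r. In the simulated setting, half of the acquisition variance is stable and recall noise is independent between sessions. The acquisition difference then has variance 2 × 0.5 = 1 and the recall difference r² + 2(1 − r²) = 2 − r². So ρ = r/√(2 − r²), and r = 0.5 gives 0.5/√1.75 = 0.38. Other structures give other values.

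**5. Generalization.** A session's acquisition score is the same in all three recall contexts. As a main effect it leaves the context-interaction tests unchanged in complete sessions; only its interaction with context can alter them.

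**6. Prerequisite, only if used to exclude.** If a fraction f of sessions fails, complete pairs number 80(1 − f)² when failures are independent and 80(1 − f) when the same people fail twice. For f = 0.10 this is 65 to 72 (power 0.80 falls to 0.71–0.76); for f = 0.20 it is 51 to 64 (0.61–0.71). Both rates are assumptions.

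**The case against.** The design already has a control for conditioning strength. CS+U is conditioned in the same session and never extinguished (Section 2.4.5.1), so CS+U vs CS+E refers recall to that session's own conditioning. This stands, and it limits the point to CS+E vs CS−. It does not dispose of it: objective 1 accepts either contrast as evidence of a deficit, and under proportional extinction CS+U vs CS+E also carries conditioning strength, in the opposite direction.

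A reader might infer that the main drug test is biased too. The documents do not support that. Medication order is double-blind and counterbalanced (Section 2.3), and acquisition precedes the capsule in each session. Second-session acquisition does follow the first-session drug, but after 4–6 weeks and with a different environment and stimulus set (Section 2.5.5).

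A reader might also infer that patients or sessions are discarded for failing the SER criterion. No exclusion rule is written, the level at which the criterion applies is not given, and the supplement on psychophysiological analysis (S13) is not shown. Data loss is a possibility, not a finding.

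Finally, adjustment in objective 1 changes the question. If HPA-axis dysregulation itself alters acquisition, the covariate removes part of the group difference. That stands, and is the reason to report both estimates. The distortion is also modest beside the roughly 0.63 SD detectable with 80% power at 40 vs 40.

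**Conclusion.** The concern holds in limited form. The written models omit a pre-drug baseline on the same measure that is collected in both sessions. For objective 1 this leaves CS+E vs CS− open to confounding by conditioning strength: about 0.09 to 0.25 SD, with a type I error of 0.07 to 0.20, for assumed correlations of 0.3 to 0.5 and group gaps of 0.3 to 0.5 SD. If the groups acquire equally there is no distortion. For objective 2 there is no bias. A precision gain is possible, but its size depends on a correlation of session differences that no document gives.

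It would go too far to say that stronger conditioning always passes for weaker extinction memory, or that the plan loses usable data. The first fails on CS+U vs CS+E; the second rests on an exclusion rule that the article does not state.

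**What to change.** Add to each recall model the last-block acquisition differential (CS+s minus CS−) of the same measure from the same session.

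- **Objective 1:** report the adjusted and unadjusted group differences side by side. State that the adjusted one compares extinction memory at equal acquisition.
- **Objective 2:** split the covariate into the person's mean over both sessions and the session's deviation from it; the deviation is what can sharpen the drug contrast.
- **Generalization models:** include the covariate's interaction with context.
- **Prerequisite:** state whether failing the SER criterion excludes anything, and at what level. If it does, add a mixed-model analysis of all usable sessions.

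The cost is analysis wording, a few degrees of freedom and a second reported estimate for objective 1. No new data are needed.
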